### Procedures

Figure 1 shows the study flow and data collection points of the NYCKidSeq project. This includes a lead-in phase of the first 30 participants and the subsequent RCT. The first 30 families who met eligibility requirements and agreed to participate were entered into the lead-in phase of the study. All other participants are enrolled into the RCT and randomized to either the SOC or the GUÍA study arm.

#### Lead-in phase

The participants of the lead-in phase (*N* = 30) were not randomized to a study arm. Instead, they were asked to provide feedback on the surveys or on GUÍA. Participants in the lead-in phase completed the same series of study visits as those in the RCT phase (study visits are described in detail below).

The first 15 participants received genomic results with genetic counseling using GUÍA. After their result session, a trained study team member collected participant feedback on GUÍA using a brief, structured feedback guide to explore parents’ reactions to GUÍA. Feedback was used to address and clarify wording/phrasing, use of images, order of information, amount and detail of information, pace, and potential Spanish translation issues.

The next 15 participants provided input about the surveys. After each study survey was administered, a trained member of study staff gathered participant feedback on the survey using a “think aloud” format. Participant feedback focused on survey question clarity, flow, and order. These participants received genomic results using SOC genetic counseling.

#### Randomized controlled trial

Participants in the RCT (*N* = 1100) are randomized using a stratified randomization scheme by disease category (cardiac, neurologic, immunologic) and clinical site as seen in Fig. 2. Randomization occurs prior to the baseline visit (BL) via a randomization module in REDCap applied by a study staff member. The REDCap randomization allocation is not revealed to study staff at any point in the study.

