**Fig. 1 Fig1:**
[figure not shown]
NYCKidSeq study design. The NYCKidSeq study involves two phases, a lead-in phase and a randomized controlled trial (RCT). Participants in both phases receive TGP and WGS testing and complete surveys at baseline, after result disclosure (ROR1 survey), and 6 months after result disclosure (ROR2 survey). In the lead-in phase, participants (*N* = 30) are enrolled into either the GUÍA feedback arm where participants complete a structured feedback interview after completion of the ROR1 survey or survey feedback arm where participants provide survey feedback after completing each survey. In the RCT phase, participants (*N* = 1100) are randomized to the GUÍA arm or the standard of care arm (SOC). Participants in the GUÍA arm receive result disclosure from genetic counselors using GUÍA versus participants in the SOC arm who receive SOC genetic counseling

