### Study population

#### Recruitment, enrollment, and sample size

Potential participants are receiving medical care under a physician at a participating institution (MS or EM). Participants and their families are introduced to the study by their physician during a routine clinic visit, phone call, or during an in-patient admission. Potential participants who express interest in the study and verbally consent to being contacted by study staff are referred to the study team. Study staff confirms the participant’s eligibility and obtains informed consent to complete the baseline parental survey during an in-person encounter. Surveys are conducted in either English or Spanish, depending on participant preference. Informed consent for WGS and TGP testing is obtained by a genetic counselor during an in-person baseline encounter in the participant’s preferred language (English or Spanish), and assent is obtained from capable children. Enrollment is achieved after a blood draw for the proband’s sample for genetic testing has been collected. At the same time, blood is drawn from biological parents. If one or more biological parents are not available during the visit, a saliva kit is mailed to the home to collect a saliva sample. The enrollment target is 1130 participants, including the lead-in phase. Participants enrolled in the RCT receive $80 in gift cards for completing all three study visits and those enrolled in the lead-in phase receive $120 in gift cards. Referring physicians do not receive compensation for their participation.

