### Study outcomes

#### RCT survey measures

The NYCKidSeq project is assessing participant outcomes through surveys administered at BL, prior to pre-test counseling and consent for the genomic testing, following the result disclosure genetic counseling during ROR1, and 6 months after disclosure of results at ROR2. The primary study outcome is the participant’s perceived understanding of genomic testing results, with comparison of results in SOC arm to GUÍA arm. The secondary study outcomes are objective understanding of genomic testing results and understanding of medical follow-up, the actionability of genomic results, and adherence to medical follow-up recommendations, with comparison of results in SOC arm to GUÍA arm. Additional participant outcomes focus on six domains: (a) attitudes toward genomic testing, (b) perceived utility, (c) psychological, (d) behavioral, (e) social, and (f) economic impact of genomic testing. With the exception of economic impact, all outcomes will be compared between the two study arms. The CSER consortium harmonized survey measures so that CSER projects, when possible, administer standardized survey measures [25] to facilitate combining data into a single data set for cross-consortium analysis. Table 2 summarizes participant outcomes being assessed across the three time points. When possible, previously validated measures were used. The BL and ROR1 surveys are administered in-person by a study staff member while the ROR2 survey is administered by a study staff member over the phone or video. Surveys are administered in either English or Spanish. All survey response data is entered and maintained in the REDCap database.

**Table 2 Tab2:** NYCKidSeq participant outcomes by survey timepoint

Variable	Source	BL^**1**^	ROR1^**2**^	ROR2^**3**^

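### Families are randomised before consent, baseline survey and enrolment, so arm-dependent loss is possible before enrolment and the randomised, enrolled and analysed numbers match only if no family is lost

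*Protocol article*

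**What the plan says.** The section on the randomized controlled trial places allocation first: "Randomization occurs prior to the baseline visit (BL) via a randomization module in REDCap applied by a study staff member".

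The section on recruitment, enrollment and sample size describes what a family has agreed to by then. Interested families who "verbally consent to being contacted by study staff are referred to the study team". Staff then confirm eligibility and the study "obtains informed consent to complete the baseline parental survey during an in-person encounter". "Informed consent for WGS and TGP testing is obtained by a genetic counselor during an in-person baseline encounter", and "Enrollment is achieved after a blood draw for the proband’s sample for genetic testing has been collected".

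The text after Fig. 2 adds that the counselor giving pre-test counseling at the baseline visit is assigned to the family's arm, and that only families who consent to testing go on to sampling. Under RCT survey measures, the baseline survey is among the "surveys administered at BL, prior to pre-test counseling and consent for the genomic testing".

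The intervention comes later. According to the Fig. 1 legend, "Participants in the GUÍA arm receive result disclosure from genetic counselors using GUÍA", and the study design overview puts that visit at about 3 months.

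Two pairs of statements disagree:
- **Order.** The opening of Procedures says that families are enrolled into the RCT and then randomised. The recruitment and RCT sections read together give the reverse.
- **Awareness.** The RCT section says that study staff are never shown the allocation. The limitations paragraph of the Discussion says that participants and study staff know it.

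**The concern.** Randomisation protects the comparison from the moment of allocation onwards. Here a consent decision and a blood draw stand between allocation and enrolment, and the counselor working at that point differs by arm. If one arm's counselors lose more families than the other's, and the lost families differ in ways related to understanding of results, the enrolled groups are no longer comparable. That could affect the primary comparison of perceived understanding.

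The stated sample size hides the gap, because the same 1100 serves as the number randomised, enrolled and analysed. A lesser issue is that the baseline scales are collected after allocation.

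**Working it through.** **1. The plan's own numbers.**
- Enrollment target, from the recruitment section: 1130 including 30 lead-in families, so 1130 − 30 = 1100 enrolled in the RCT.
- Number randomised, from the RCT section: 1100.
- Number analysed, from the RCT analysis paragraph: 550 per arm, so 2 × 550 = 1100.

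All three agree. They can do so only if every randomised family reaches blood draw.

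**2. Sequence.** Reading the sections together:
1. verbal agreement to contact, and eligibility check;
2. randomisation;
3. survey consent and baseline survey;
4. pre-test counseling by the arm's counselor, and testing consent;
5. blood draw, which is enrolment;
6. result disclosure, with or without GUÍA, at about 3 months.

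The article does not name the survey-consent encounter as the baseline visit. However, the baseline survey is completed at that visit, and no earlier in-person contact with study staff is described. Steps 3 to 5 lie between allocation and enrolment, and step 4 can differ by arm.

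**3. Number to randomise in order to enrol 1100.** N = 1100 / (1 − loss), rounded up. The loss rates are assumptions, because the article gives none.

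| Assumed loss | 1100 / (1 − loss) | Families to randomise |
|---|---|---|
| 5% | 1157.9 | 1158 |
| 10% | 1222.2 | 1223 |
| 15% | 1294.1 | 1295 |

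**4. Bias from unequal loss.** Let d be the mean outcome gap, in SD units, between enrolled and non-enrolled families, the same in both arms. Let L be an arm's loss. The mean among enrolled families then exceeds the mean of all randomised families by L × d. With no true effect, the bias in the arm difference is (difference in L) × d.

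The standard error with 550 per arm is √(2/550) = 0.0603 SD. Type I error is Φ(−1.96 − bias/SE) + 1 − Φ(1.96 − bias/SE), taking a two-sided 5% test. The article does not state sidedness.

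| Difference in loss | d (assumed) | Bias (SD) | Type I error |
|---|---|---|---|
| 0 points | any | 0 | 5.0% |
| 5 points | 0.25 | 0.0125 | 5.5% |
| 5 points | 0.5 | 0.025 | 7.0% |
| 5 points | 0.8 | 0.04 | 10.2% |
| 10 points | 0.25 | 0.025 | 7.0% |
| 10 points | 0.5 | 0.05 | 13.2% |
| 10 points | 0.8 | 0.08 | 26.4% |

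For scale, the difference detectable with 550 per arm at an assumed 80% power is 0.0603 × (1.960 + 0.842) = 0.169 SD. A bias of 0.05 SD is about 30% of that (0.05 / 0.169).

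**5. Baseline data.** Table 2 shows no baseline measurement of perceived understanding, the primary outcome. The covariates named in the RCT analysis paragraph are age, sex and race/ethnicity, which allocation does not change. What is exposed is the set of scales measured at baseline, such as decisional conflict, attitudes toward genetic testing and PHQ-8.

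**The case against.** The strongest reply is that the route to bias is possible but not shown. No loss by arm is reported. The consent process is described once for both arms, GUÍA appears only at disclosure, and the only arm difference described at the baseline visit is which counselor the family meets. The baseline survey comes before that counselor acts. Equal, non-selective loss would do no harm. All of this stands, and it limits the point to a risk that the design permits.

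A reader might go further in four ways that the article does not support:
- **That everyone knows the arm at the baseline visit.** The RCT section says that staff are not shown the allocation. The Discussion says that staff and participants are aware, but explains this by questions about the experience of using GUÍA, which comes later. The statements conflict, and neither settles what is known at baseline.
- **That non-enrolled families are dropped and the intention-to-treat denominator is lost.** No sentence says so; it is an inference from the matching numbers. Analysis sets may be defined in the full protocol or the SAP, which are not shown.
- **That 1100 randomised cannot equal 1100 enrolled.** It can, if no family is lost.
- **That early allocation has no purpose.** Assigning counselors by arm from the first visit requires the arm to be known by then. It is a trade-off, although GUÍA itself does not need it.

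The reply does not remove the consent step that follows allocation, or the contradictions about order and awareness. These are in what the article itself fixes.

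**Conclusion.** The point holds as a design weakness that should be corrected. Allocation precedes survey consent, testing consent and enrolment, with an arm-assigned counselor in between, although the arms are meant to differ only at disclosure about 3 months later. The stated numbers leave no room for families lost on the way.

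The size is unknown. With the assumed 0.5 SD gap, a 5- or 10-point difference in loss gives a bias of 0.025 or 0.05 SD and a type I error of about 7% or 13%; with no difference in loss it is zero. These figures rest on assumed loss rates, an assumed gap that is equal in both arms, and a two-sided 5% test. They show what the design allows and say nothing about what has happened.

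A reader might infer that all baseline data are compromised. That is too strong: the primary outcome and the named covariates are essentially untouched, and the issue is minor for the remaining baseline scales.

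**What to change.** **Families not yet randomised.** Run the existing REDCap module after consent, baseline survey and blood draw, and before result disclosure. Leave enough time for counselors to prepare the personalised GUÍA content. Record the date of the change so that the two periods can be distinguished in analysis.

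**Families already randomised.** Define the analysis population from randomisation. Report losses between randomisation and blood draw by arm, and give the number randomised separately from the number enrolled. A family that never had testing has no results to understand, so state how the missing outcome is handled.

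**Text.** Reconcile the recruitment section, the opening of Procedures, the RCT section (including the text after Fig. 2) and the Discussion on two matters: the order of enrolment and randomisation, and who knows the allocation and when.

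**Cost.** A protocol amendment and a change in when an existing module is run. Some families may have a different counselor at disclosure than at pre-test counseling. Because recruitment began in January 2019, the trial would contain two cohorts with different randomisation points. The reporting and text changes need no change in conduct.

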**Fig. 2 Fig2:**
[figure not shown]
Randomization schema

At the BL visit, participants complete the baseline surveys with a study staff member and receive pre-test genetic counseling by a genetic counselor designated to their arm. The consenting process consists of the family being educated about the study; the risks, benefits, and limitations of genomic testing; purpose of genomic testing; possible results of genomic testing including the option to receive or decline secondary findings; and potential implications for other family members. As part of the pre-test genetic counseling, the genetic counselor obtains a medical and family history. Families who consent for testing undergo blood or saliva collection for both TGP and WGS. Parents and cognitively intact young adults will also provide permission to use of de-identified samples in future research; sharing of de-identified data in secure, public research databases; and to be contacted by trial investigators for further informational and consent-related purposes. Participants consenting to take part in this study voluntarily agree to indefinite storage of their and their child’s blood and sequencing information by the research study, including NYCKidSeq research teams at Sema4, NYGC, EM, and MS. Samples may be used for either research or clinical purposes if additional testing is needed. Participants can decide to withdraw consent for the storage of their or their child’s biological samples at any time by contacting the principal investigator. Sample(s) or portions thereof that have not already been used will be destroyed; however, the parent or child’s sample may have already been distributed to other researchers within NYCKidSeq before the request to destroy was received and may not be able to be retrieved.

Once a participant’s results are reported, generally after 3 months, the results are sent to the genetic counselor. Results are reviewed and shared with the referring physician and/or a geneticist who then shares their interpretation about the significance of the genomic findings as well as their medical recommendations with the genetic counselor. An ad hoc discrepancy committee is available to review cases at the discretion of the genetic counselor for cases that have discrepant or unsatisfying results. The committee consists of NYCKidSeq medical geneticists, genetic counselors, laboratory directors, and referring providers. The decision of the discrepancy committee is used as a final diagnostic determination.

Each participant has a one-on-one result disclosure visit with a genetic counselor (ROR1). The referring physician can also participate in the appointment at their discretion. At the result disclosure appointment, the participant is informed of the results and their referring provider’s medical recommendations. The method of genetic counseling delivery depends on the study arm to which the participant is randomized. After genetic counseling, participants immediately complete the ROR1 survey with a study staff member. Six months after the ROR1 visit, approximately 9 months after study entry, a follow-up visit (ROR2) occurs either by phone or video. During this interaction, a study staff member administers the final survey (ROR2 survey).

Each subject’s genetic results may be reviewed every 12 months for the duration of the study. This is because information about genetic variants can change over time, as can the patient’s phenotype. As both types of information contribute to making a diagnosis, a re-analysis that recognizes reclassification of DNA sequence variants in a patient and their current phenotypic presentation can combine to change their original diagnosis. Variant reclassification information is derived by the laboratory from public databases such as ClinVar, while the refined phenotypic information is prompted by and entered into GenomeDiver following a review of electronic medical records. If results are reinterpreted, a new visit is arranged to inform the family of the finding. The visit to review the results is performed by a genetic counselor.

#### Pilot study

We will also recruit 20 referring providers, 6 genetic counselors, and 7 laboratory staff members for our GenomeDiver pilot study. Two different interventions will be performed. One is retrospective and facilitates updating participants’ phenotypic information 12 months after ROR1 to help with the review of the original diagnostic laboratory report. The second intervention is part of the ongoing recruitment of patients and occurs as part of the primary analysis of the patient’s genomic sequence. We randomize these patients into two arms, one with SOC, the other with the addition of a GenomeDiver intervention. Following the generation of the annotated Variant Call Format (VCF) file, the clinicians (referring provider and genetic counselor assigned to the patient) are contacted and requested to perform a GenomeDiver session. HPO terms that help to discriminate the variants with the highest Exomiser combined scores [33] are presented to the clinicians and categorized as present, absent, or uncertain for that patient. Potential phenotypes present in the patient are then displayed for clinician evaluation and possible flagging, and the enhanced, updated information is then returned to the diagnostic laboratory.

### Study outcomes

#### RCT survey measures

The NYCKidSeq project is assessing participant outcomes through surveys administered at BL, prior to pre-test counseling and consent for the genomic testing, following the result disclosure genetic counseling during ROR1, and 6 months after disclosure of results at ROR2. The primary study outcome is the participant’s perceived understanding of genomic testing results, with comparison of results in SOC arm to GUÍA arm. The secondary study outcomes are objective understanding of genomic testing results and understanding of medical follow-up, the actionability of genomic results, and adherence to medical follow-up recommendations, with comparison of results in SOC arm to GUÍA arm. Additional participant outcomes focus on six domains: (a) attitudes toward genomic testing, (b) perceived utility, (c) psychological, (d) behavioral, (e) social, and (f) economic impact of genomic testing. With the exception of economic impact, all outcomes will be compared between the two study arms. The CSER consortium harmonized survey measures so that CSER projects, when possible, administer standardized survey measures [25] to facilitate combining data into a single data set for cross-consortium analysis. Table 2 summarizes participant outcomes being assessed across the three time points. When possible, previously validated measures were used. The BL and ROR1 surveys are administered in-person by a study staff member while the ROR2 survey is administered by a study staff member over the phone or video. Surveys are administered in either English or Spanish. All survey response data is entered and maintained in the REDCap database.

**Table 2 Tab2:** NYCKidSeq participant outcomes by survey timepoint

Variable	Source	BL^**1**^	ROR1^**2**^	ROR2^**3**^
**Primary outcome**				
*Perceived understanding of genomic testing results*	NYCKidSeq developed measure (novel)	**–**	**X**	**X**
**Secondary outcomes**				
*Objective understanding of genomic testing results*	NYCKidSeq developed measure (novel)	**–**	**X**	**X**
*Medical actions and non-medical/patient-initiated actions attributable to genomic testing*	CSER developed measures (novel): Attributable to Genomic Testing (RMA) and Patient-Initiated Actions Attributable to Genomic Testing (PIA)	**–**	**–**	**X**
**Attitudes**				
*Satisfaction with the mode of delivery*	CSER developed measure (novel) adapted from Patient Assessment of cancer Communication Experiences (PACE) [34, 35]	**–**	**X**	**–**
*Satisfaction with results*	Satisfaction with information about medicine (SIMS) [36]	**–**	**X**	**–**
*Attitudes toward genetic testing*	Adapted from Genetic testing to Understand and Address Renal Disease Disparities (GUARDD) study [37, 38]	**X**	**X**	**X**
*Empowerment*	Adapted from GUARDD study [37]	**X**	**X**	**X**
*Decisional conflict*	Decisional Conflict Scale (Low Literacy) [39]	**X**	**X**	**X**
**Perceived utility**				
*Impact of genomic testing on health status*	Functional status II-R (child) [40]	**X**	**–**	**X**
*Impact of genomic testing on quality of life*	Child Health Utility Instrument (CHU9D; parent as proxy) [41]; SF-12 health survey (for parent) [42]	**X**	**–**	**X**
*Clinical utility*	Patient-reported utility (PrU) [43]	**–**	**X**	**X**
